## Abstract

**Background:**

Despite high pre-exposure prophylaxis (PrEP) awareness and willingness among Chinese men who have sex with men (MSM), actual uptake remains critically low. The health action process approach (HAPA) is a 2-phase theory that addresses both the motivational and volitional phases of health behavior change, making it suitable for tackling the intention-behavior gap in PrEP use. In China, where PrEP is not covered by national health insurance, financial barriers further hinder uptake. Group-based conditional economic incentives (GCEIs) represent an innovative strategy to address cost-related disincentives by leveraging peer influence.

**Objective:**

This randomized controlled trial aims to evaluate the effectiveness of HAPA-driven interventions, both alone and combined with GCEI, to enhance PrEP initiation and adherence among high-risk, PrEP-naive MSM in China.

**Methods:**

High-risk HIV-negative MSM naïve to PrEP were recruited via community-based organizations in 3 Chinese cities. Participants underwent individual randomization to 3 arms: (1) HAPA-based cognitive behavioral intervention featuring tailored WeChat messages and 2 structured motivational interviews targeting stage-specific barriers; (2) combined HAPA intervention with GCEI linked to peer group initiation rates, incorporating facilitated offline group activities; or (3) standard care control receiving nonpersonalized HIV prevention information. The physician-prescribed PrEP initiation rate at 3 months serves as the primary outcome. Secondary outcomes include PrEP adherence, HIV risk perception, PrEP-related stigma, and intervention acceptability. Analysis follows intention-to-treat principles using mixed-effects models.

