### Outcomes

The primary outcome indicator of this study is the rate of PrEP initiation, based on formal PrEP prescriptions issued by doctors. The secondary outcome indicators include medication adherence rates after initiating PrEP (based on self-reported adherence and the medication calendar in the mini-program), intention to pay for PrEP (for 3 types of PrEP), PrEP stigma, changes in condom use, and changes in number of sexual partners before and after PrEP use.

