Intervention process and satisfaction evaluation: This evaluates participants’ experience and satisfaction with the mobile health intervention platform (the WeChat mini-program), including usage frequency, overall satisfaction, willingness to recommend it, and specific feedback on its ease of use, interface design, information resources, medication reminders, recording functions, and data privacy protection.Risk compensation behavior assessment: It investigates changes in participants’ sexual behavior patterns during the intervention to assess the possibility of risk compensation, including changes in the frequency of same-sex intercourse, number of male sexual partners, and condom use frequency compared to baseline.PrEP uptake status: Based on the current PrEP status at follow-up, it further explores specific reasons for noninitiation or discontinuation, sources of medication acquisition, methods of recording medication use, episodes of treatment interruption, occurrence of adverse drug reactions, partner awareness, psychological experiences related to PrEP use, and willingness to recommend it.Dynamic measurement of PrEP-related cognition: It reapplies key items from the validated HAPA-based PrEP cognition scale to assess changes in postintervention cognition, including self-efficacy for PrEP initiation and maintenance, positive and negative outcome expectations, perceived HIV risk, and action planning.Reassessment of PrEP decision and payment willingness: It re-evaluates participants’ perception of pricing and willingness to use different PrEP regimens at market prices, as well as their views on potential models for cost-sharing.Follow-up on PrEP perceived stigma and MSM group cohesion: It uses a brief mental health scale to assess emotional states over the past week, remeasures PrEP perceived stigma levels, and evaluates changes in perceived cohesion within the MSM community.

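### The secondary outcome on sexual partners (and perhaps condom use) is worded so that it exists only for men who start PrEP, and the Abstract and Outcomes section name different secondary outcomes

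*Protocol article*

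**What the plan says.** Four places in the protocol article bear on this point.

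- **Abstract, Methods:** "Secondary outcomes include PrEP adherence, HIV risk perception, PrEP-related stigma, and intervention acceptability".
- **Outcomes:** "The secondary outcome indicators include medication adherence rates after initiating PrEP", followed by intention to pay for PrEP and then "PrEP stigma, changes in condom use, and changes in number of sexual partners before and after PrEP use".
- **Measurements and Follow-Ups**, on risk compensation: "It investigates changes in participants’ sexual behavior patterns during the intervention to assess the possibility of risk compensation". The items are frequency of same-sex intercourse, "number of male sexual partners, and condom use frequency compared to baseline". The same section also collects satisfaction ("Intervention process and satisfaction evaluation: This evaluates participants’ experience and satisfaction with the mobile health intervention platform") and re-measures HAPA cognition, including "positive and negative outcome expectations, perceived HIV risk, and action planning".
- **Evaluation of Intervention Effectiveness:** primary and secondary outcomes are analysed with mixed-effects models by intention to treat, with every randomised participant included and effects reported as adjusted comparisons between groups.

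The inclusion criteria (Study Population and Participant Recruitment) also matter here: nobody may have used PrEP before entry.

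**The concern.** There are two separate inconsistencies.

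The first is one of definition. A man who never starts PrEP has no period after PrEP use, so the outcome as worded has no value for him. In a PrEP-naive sample this restricts the outcome to initiators. Starting PrEP is what the interventions aim to change and, measured by prescription, it is the primary outcome. A comparison of arms among starters would condition on an event after randomisation. Men who start because of an interview or a group incentive may differ in sexual behaviour from the few who start under standard care, so a difference between arms, or the lack of one, could reflect who started rather than what the intervention did. The outcome bears on safety, because it addresses whether risk behaviour rises.

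The second is one of status. Two places in the article designate secondary outcomes and they name different sets. A reader checking the final report against this article could not tell which measured variables had secondary status.

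**Working it through.** **1. The two secondary lists side by side**

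| Outcome | Abstract | Outcomes section |
|---|---|---|
| Adherence | yes | yes |
| PrEP stigma | yes | yes |
| HIV risk perception | yes | no |
| Intervention acceptability | yes | no |
| Intention to pay | no | yes |
| Condom use | no | yes |
| Number of partners | no | yes |

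The lists have 4 and 5 items. They share 2, so there are 4 + 5 − 2 = 7 distinct outcomes. Two are only in the Abstract and three only in the Outcomes section.

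**2. The two definitions of sexual-behaviour change**

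| | Outcomes section | Measurements and Follow-Ups |
|---|---|---|
| Reference point | start of PrEP use | baseline |
| Who has a value | men who start PrEP | any participant followed up |
| Fits analysis of all randomised | no | yes |

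**3. Planning rates, checked against the plan's own figure**

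Inputs from the sample size paragraph: p₁ = 0.05, p₂ = 0.20, two-sided α = 0.05, power 90%. With p̄ = 0.125:

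n = [1.960 × √(2 × 0.125 × 0.875) + 1.282 × √(0.05 × 0.95 + 0.20 × 0.80)]² / 0.15² = (0.917 + 0.584)² / 0.0225 ≈ 100.1, or 101 rounded up.

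The stated minimum of 100 per group is reproduced, so these are the rates that the plan used.

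**4. How many men would have a before/after contrast**

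Assumptions: the planning usage rates stand for the proportion starting PrEP, and the 20% applies to each active arm. Arm sizes are from Participant Recruitment.

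- HAPA: 128 × 0.20 = 25.6
- HAPA+GCEI: 126 × 0.20 = 25.2
- Control: 127 × 0.05 = 6.35
- Total: 57.15 of 381 = 15%

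With the planned 15% attrition (× 0.85) these become about 22, 21 and 5: about 49 men, against about 324 followed up under the baseline definition.

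**5. What that does to precision (illustration)**

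For a standardised continuous outcome at 80% power, the detectable difference is (1.960 + 0.842) × √(1/n₁ + 1/n₂).

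- Initiators, 25.2 against 6.35: 2.802 × √0.1972 = 1.24 SD
- Full arms, 126 against 127: 2.802 × √0.0158 = 0.35 SD
- Full arms after attrition, 107 against 108: 0.38 SD

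These figures describe precision only. The selection problem in the initiator comparison would remain at any sample size.

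**The case against.** The strongest reply is that the article already provides for a sound comparison. The text that names risk compensation is in Measurements and Follow-Ups. It covers participants generally against baseline, and Statistical Analysis compares groups in everyone randomised. A reader might infer from the Outcomes wording that risk compensation will not be a randomised comparison in this trial. The documents do not support that: these two sections together permit one. Nor does the Outcomes section say that arms will be compared among initiators, since it names no analysis population. What stands is narrower: the outcome as worded there does not fit the only analysis population that the article states.

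Grammar is a second reply. The before/after phrase may attach only to number of partners. If so, the conflict remains for that outcome, and the Outcomes section gives condom use no reference point.

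Third, both lists are introduced by a verb that does not claim completeness, an abstract may abbreviate, and a full protocol or analysis plan not shown may fix the list. Abbreviation explains omissions from the Abstract, but not two outcomes named there and absent from the fuller section. A reader might go further and infer that outcomes will be picked after the results are known. Nothing in the documents shows this; it is a risk that an unreconciled list leaves open.

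Finally, Measurements and Follow-Ups describes questionnaire content and designates no secondary outcome, so it may simply be how the listed outcome is measured. If that is the intention, the Outcomes wording should say so.

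**Conclusion.** The point holds as two wording defects that need reconciling. First, change in number of partners, and on one reading condom use, is defined as a secondary outcome in a way that exists only for men who start PrEP. It therefore cannot be analysed as Statistical Analysis requires, and it disagrees with the baseline-referenced measurement described elsewhere. Taken literally, it would rest on about 57 of 381 men, about 6 of them in control. Those counts assume 20% starting in each active arm, 5% in control and no attrition; the conflict between the sections does not depend on them. Second, the Abstract and the Outcomes section share only 2 of 7 named secondary outcomes.

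The primary outcome is untouched. The defect does not make a randomised comparison of risk compensation impossible and does not show selective reporting. It is still worth correcting, because one secondary outcome bears on safety and the published text does not fix what it is.

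**What to change.** Before outcome data are seen:

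1. In Outcomes, define change in condom use and change in number of sexual partners as change from baseline to the scheduled follow-ups in all randomised participants, compared between arms in the mixed model already planned. Keep the contrast of before against after starting PrEP as a description of initiators only, with no inference between arms.
2. Reconcile the Abstract and Outcomes to one secondary list, and label any other measured item exploratory.

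The cost is protocol wording. Sexual behaviour is in the baseline questionnaire, and the follow-up questionnaire covers the same behaviours with no stated restriction to PrEP users, so no new data are needed. The downside is that some items named in only one list may become exploratory, which is for the trial team to decide. The article reports that outcome data were still to be collected as of February 2026, with final follow-up in August 2026 and database lock in December 2026. A dated change is most credible if made before outcome data are examined.

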**Results:**

The study protocol received ethics approval in December 2024 and was funded in December 2025. As of August 2025, 3 community-based organizations in Mianyang, Zibo, and Hohhot have agreed to participate. Preliminary testing has led to refinements in the WeChat mini-program, questionnaires, and motivational interview scripts. Data collection commenced in October 2025 and is projected to be completed by August 2026. As of February 2026, baseline recruitment is complete, with 381 eligible participants enrolled and randomized. The baseline characteristics were balanced across the 3 arms. Outcome data will be collected after the intervention. Data analysis is ongoing, with full results expected to be published before December 2026.

**Conclusions:**

This study rigorously tests a novel intervention integrating the HAPA with a GCEI model. By addressing both individual cognitive-behavioral barriers and financial disincentives within a supportive group context, this approach offers a potentially scalable strategy to bridge the PrEP uptake gap in China. Findings will provide critical evidence on combining theory-driven behavioral techniques with peer-group economic incentives for HIV prevention.

## Introduction

The burden of AIDS remains substantial. It is estimated that 0.7% (95% uncertainty interval 0.6‐0.8%) of adults aged 15‐49 worldwide are living with HIV, with a higher prevalence of 7.5% among men who have sex with men (MSM) [1]. In China, by the end of 2023, there were 1.3 million people living with HIV or AIDS, with a cumulative death toll of 458,000 [2]. The incidence of new HIV infections among MSM in China is 5.6 per 100 person-years [3]. The risk of HIV transmission remains significant, necessitating effective measures among groups at high risk, such as MSM, to control the spread of the epidemic [4].

Pre-exposure prophylaxis (PrEP) is an efficient biological prevention method to prevent HIV infection [5]. In most high-income countries, the overall PrEP usage rate among high-risk groups ranges from 28% to 80% [6]. Currently, international recommendations for MSM include oral tenofovir disoproxil fumarate or emtricitabine and long-acting injectable-PrEP (LAI-PrEP), both of which have been proven to effectively reduce the risk of HIV infection [3,4]. China has made significant efforts to promote PrEP among high-risk groups, such as launching pilot projects and approving generic medicine [7]. However, low willingness to use oral PrEP among key populations [5], stemming from cognitive biases, leads to low PrEP adoption despite potentially high demand [8]. There are over 12 million MSM in China [9], with PrEP awareness rates ranging from 41% to 86% [10,11], and approximately 65.8% to 84.9% of MSM willing to accept PrEP [12,13]. A survey of 2388 MSM across 6 Chinese cities showed that only 13.9% had used PrEP in 2022 [14]. Factors such as low health literacy, low behavior control, distrust in PrEP efficacy, lack of knowledge about PrEP, high costs, discrimination, and stigma are major barriers to PrEP use despite high demand [15,16]. Among those who initiate PrEP, its protective efficacy depends on sufficiently high adherence [17,18]. PrEP adherence rates among MSM in China range from 29.9% to 41.1% [19,20]. For LAI-PrEP, the long-acting injectable cabotegravir was approved in China in May 2024, and its usage intention and behavior among key populations are still being explored [7].

Behavioral interventions to promote PrEP among groups at high risk need to focus on increasing initiation rates before initiation and improving adherence after initiation. Existing interventions to promote PrEP initiation among MSM include PrEP health education [21], motivational structured interviews [22], MSM peer education and guidance [23], and mobile health technology interventions [24]. In China, smartphone-based interventions and app-based PrEP initiation interventions have shown some effectiveness, with PrEP initiation rates ranging from 65% to 89% [25]. The health action process approach (HAPA) is a 2-phase theory that divides behavior into the preintentional motivational phase (focusing on promoting the generation of behavioral intention) and the postintentional volitional phase (focusing on translating intention into behavior, maintaining behavior, and managing relapse) [26]. The HAPA phase model can effectively address the high willingness–low usage gap in PrEP and is particularly suitable for explaining and measuring low willingness, low usage rates, low adherence, and low reinitiation rates after discontinuation at different PrEP stages. Chan et al [27] used motivational structured interviews to improve PrEP initiation rates, with the core of the intervention being to explore and strengthen individuals’ intrinsic motivation to use PrEP and improve self-efficacy through situational simulation. Clarifying the suitability of PrEP and risk behavior is key to further effective PrEP intervention [28].

In China, where PrEP medications are not yet covered by national health insurance, financial barriers significantly hinder uptake among MSM despite high willingness. The out-of-pocket cost for oral PrEP (eg, approximately US $5.5 per on-demand dose) poses a critical obstacle, particularly for low-income individuals. In China, the monthly cost of domestically produced generic oral PrEP is approximately ¥200‐300 (US $28‐$42); for on-demand dosing, the cost per use is about ¥40 (US $5.6). This context underscores the need for innovative strategies to mitigate cost-related disincentives. Group-based conditional economic incentives (GCEIs) offer a promising solution by leveraging behavioral economics principles. GCEI capitalizes on peer influence and shared accountability, addressing both financial and social barriers [29,30]. For MSM, whose health behaviors are often shaped by community norms, GCEI can amplify motivation through collective goal-setting (eg, group-level initiation targets) and tiered rewards (eg, US $22 for 80%‐100% group adherence). Prior studies demonstrate GCEI’s efficacy in improving antiretroviral therapy adherence among youth, suggesting translatability to PrEP promotion [31-33]. By integrating financial incentives with peer dynamics, GCEI aligns with China’s need for scalable, cost-sensitive interventions to bridge the intention-behavior gap in PrEP uptake.

Existing research on PrEP uptake among Chinese MSM has largely relied on cross-sectional analyses that identify barriers but fail to translate findings into effective interventions. These studies consistently highlight structural challenges—particularly financial constraints in China’s self-pay PrEP model and pervasive stigma surrounding both HIV prevention and same-sex behaviors—yet proposed solutions rarely account for the cultural and logistical realities of this population. Our study addresses these limitations through an intervention model that combines theory-driven behavioral strategies with pragmatic delivery methods tailored to the Chinese context. The use of WeChat-based eHealth platforms proves particularly strategic, as it capitalizes on near-universal smartphone penetration among Chinese MSM while circumventing stigma through discreet, asynchronous engagement. This approach recognizes that target users may avoid clinic-based services due to privacy concerns, yet actively participate in virtual communities where health information is exchanged. By embedding the intervention within a familiar digital ecosystem and incorporating group-based incentives that leverage existing social networks, the design intentionally works with—rather than against—the lived experiences of Chinese MSM. The result is an implementation framework that simultaneously addresses individual behavioral determinants and systemic barriers, offering a realistic path to scaling PrEP access in stigma-affected populations.

This study aims to evaluate the effectiveness of HAPA-based interventions, alone and combined with GCEI, in improving PrEP initiation and adherence among Chinese MSM at high risk for HIV infection. We hypothesize that both intervention arms (HAPA and HAPA+GCEI) will outperform the standard care control in promoting PrEP initiation, with the combined HAPA+GCEI arm expected to yield the greatest efficacy.

## Methods

### Study Design

This study uses a randomized controlled trial design. The MSM-friendly community-based organizations (CBOs) are selected, and the participants are randomly allocated to the following three arms: (1) HAPA-based cognitive intervention arm, (2) the HAPA+ conditional economic incentive combined intervention arm, and (3) control arm. The intervention will last for 3 months, during which baseline data and 2 follow-up assessments will be collected. The first follow-up will occur at the conclusion of the intervention, while the second follow-up will take place three months postintervention. We will assess PrEP uptake before and after the intervention and between different study arms. We used the SPIRIT 2025 checklist to ensure completeness of the trial protocol reporting (Checklist 1).

### Study Population and Participant Recruitment

The study population is sourced from 3 MSM-friendly CBOs located in different regions. The inclusion criteria for community organizations are: (1) the organization must meet the sample size requirements for the project; (2) there must be a willingness to collaborate, making PrEP promotion a work priority; and (3) the organization should have a good partnership with local hospitals or centers for disease control and prevention to coordinate with disease control specialists and HIV specialists. Community collaborators participate in project training, assist with participant recruitment, support baseline and follow-up surveys, and help with quality control. Participants included in this study must meet the following criteria: (1) aged 18 years or older; (2) assigned male sex at birth and have had sexual intercourse with men in the past 6 months; (3) HIV negative at the start of the study; (4) no prior PrEP using experience; (5) willing to participate in the PrEP intervention and voluntarily consent to complete data collection and follow-up according to the assigned protocol; (6) classified as high risk for HIV infection in the past 6 months as suggested by the “Expert Consensus on HIV Pre-Exposure Prophylaxis in China (2023)” [7]. Participants are excluded if they meet any of the following criteria: (1) HIV positive, or unaware of their HIV status and refuse to undergo HIV testing; (2) have a health condition that makes PrEP unsuitable; and (3) have cognitive impairments or other severe illnesses that may affect the informed consent process.

The sample size calculation was based on the formula for an individually randomized controlled trial, assuming a 2-sided significance level (*α*) of .05 and type II error rate (*β*) of .10 (90% power). Based on extant literature and a 2021 multicenter PrEP survey in China indicating a median current PrEP usage rate (*p₁*) of 5% among MSM, the target post-intervention usage rate (*p₂*) was set at 20%. This yielded a minimum requirement of 100 participants per group. Accounting for an anticipated 15% attrition rate, the sample size was increased to 126 participants per group, resulting in a total target enrollment of 378 participants (126 per group) across 3 CBOs.

The randomization sequence was generated by an independent statistician using simple randomization. The sequence was then integrated into the backend of the customized WeChat mini-program. After a participant completed the baseline survey and was confirmed eligible, the system automatically executed the group assignment. Allocation concealment was strictly implemented. After a participant completed the baseline assessment and was confirmed eligible, the system automatically executed the group assignment based on the preloaded, concealed sequence. Until this point of allocation, neither the participant, the research coordinator enrolling the participant, nor the outcome assessors could access or predict the upcoming assignment. The allocation is only revealed to the system and the intervention coordinator after the participant’s baseline data is irrevocably locked and enrollment is finalized. The participants are blinded to group assignment. Outcome assessors and data analysts remain blinded to group assignment throughout the trial. They have access only to deidentified participant data coded with unique study IDs, without any information linking the ID to the intervention arm.

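### The stated 126 per group does not follow from 100 per group and 15% attrition (that gives 118), and the 5% control rate is an unlabelled proxy for 3-month PrEP initiation

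*Protocol article*

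**What the plan says.** The sample size is set out in the Protocol article under Study Population and Participant Recruitment. It uses a formula for individual randomization, "assuming a 2-sided significance level (*α*) of .05" and 90% power. The control input comes from existing literature and "a 2021 multicenter PrEP survey in China indicating a median current PrEP usage rate" "of 5% among MSM, the target post-intervention usage rate" being set at 20%. The result is given as "This yielded a minimum requirement of 100 participants per group". The next step is "Accounting for an anticipated 15% attrition rate, the sample size was increased to 126 participants per group", for a total of 378.

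The Outcomes section defines the endpoint differently from these inputs: "The primary outcome indicator of this study is the rate of PrEP initiation, based on formal PrEP prescriptions issued by doctors". The Abstract places it at 3 months. The eligibility criteria require no previous PrEP use, high risk of HIV infection, and willingness to take part in a PrEP intervention.

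**The concern.** There are two separate points.

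- **Attrition step.** Dividing 100 by the retained fraction at 15% loss does not give 126, and no other reason for 126 is offered. A reader cannot tell whether the attrition figure, the base or the target is the intended one.
- **Planning rate.** The 5% describes how many MSM in general were using PrEP at the time of a survey. The endpoint is a new prescription within 3 months among men who have never used PrEP. The article does not say that the first stands in for the second, and it gives no control-arm initiation rate. Readers of the eventual result will take 90% power as applying to prescription initiation, and a null or borderline comparison would be interpreted in that light.

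**Working it through.** **Inputs (Study Population and Participant Recruitment).** p1 = 0.05, p2 = 0.20, two-sided alpha 0.05 (z = 1.960), power 90% (z = 1.2816), attrition 15%, stated base 100, stated target 126 per group.

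**Step 1: reproduce the base.** Pooled two-proportion formula, with mean rate p = 0.125:

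n = [1.960 × √(2 × 0.125 × 0.875) + 1.2816 × √(0.05 × 0.95 + 0.20 × 0.80)]² / 0.15²

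= [1.960 × 0.4677 + 1.2816 × 0.4555]² / 0.0225 = 100.06

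The stated 100 is reproduced (101 if rounded up). Power with exactly 100 per group is 90.0%.

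**Step 2: apply the attrition.**

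| Calculation | Per group |
|---|---|
| 100 / (1 − 0.15) = 117.6 | 118 (354 in total) |
| 100 × 1.15 (cruder rule) | 115 |
| Stated | 126 (378 in total) |

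Starting from 101 gives 119 or 117 by the same two rules. Working backwards, 1 − 100/126 = 20.6% attrition, while 126 × 0.85 = 107.1, so 126 at 15% loss would need a base of about 107. Other base formulas do not explain the figure either, because they do not give the stated 100: unpooled 97, arcsine 93, continuity-corrected 114, alpha/2 119, alpha/3 129.

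**Step 3: consequence under the stated rates.** With 107 completers per group, power = Φ{[0.15 × √107 − 1.960 × 0.4677] / 0.4555} = Φ(1.394) = 91.8%. The gap of 126 − 118 = 8 per group therefore adds power.

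**Step 4: dependence on the proxy.** The article gives no 3-month initiation rate for controls, so the rates below are assumptions. Same formula, 107 per group:

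| Assumed control rate | Power, p2 kept at 20% | Power, 15-point difference kept |
|---|---|---|
| 2% | 99% | 97% |
| 3% | 98% | 95% |
| 5% | 92% | 92% |
| 8% | 72% | 86% |
| 10% | 54% | 83% |

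Power rises below 5% and falls above it. The fall is steep in the middle column because the effect itself shrinks there: at 10% versus 20% it is 10 points rather than the planned 15.

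**The case against.** The best defence of 126 is that 100 is called a minimum and that the target exceeds what 15% loss requires, so the figures can stand together with a margin of 8 per group. There is also a natural explanation: peer groups of six spread over three community organizations suggest multiples of 18, and 126 = 7 × 18 is the first such multiple at or above 118. This disposes of any claim that attrition, size and power are mutually incompatible. It does not rescue the sentence, which names attrition as the only reason; the rounding is an inference.

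On the 5%, the defence is that nobody uses PrEP at entry, so any use at 3 months requires initiation during the trial, and use and initiation are close though not identical. Planning rates are always proxies, and the full protocol may justify this one. That is fair, and it makes this a matter of labelling rather than of an invalid calculation.

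A reader might infer more, namely that the trial is underpowered, pointing to the Introduction: "A survey of 2388 MSM across 6 Chinese cities showed that only 13.9% had used PrEP in 2022". The article does not support this. The 13.9% is itself a figure for use, from another survey and year, in men not selected as PrEP-naive, so it is no better a guide to control-arm initiation than the 5%. A rate below 5% is also plausible: controls start from zero use, receive nonpersonalized information, and must buy PrEP at market price.

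**Conclusion.** The point stands as a reporting error plus an unlabelled assumption. The sentence on attrition is wrong as written: the stated inputs lead to 118 per group (354), and 126 (378) corresponds to 20.6% loss. The error is conservative. If loss is 15% and the rates are 5% and 20%, the trial has about 92% power and meets its 90% target.

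The 90% figure is conditional on a prevalence of current use standing in for 3-month initiation. The direction of any resulting error is unknown, and underpowering is not shown. The sensitivity figures rest on assumed control rates, 107 completers per group and a simple two-group comparison of proportions.

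**What to change.** Replace the attrition sentence with one of two statements, whichever reflects what was done:

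- 126 per group allows for about 20% attrition from a requirement of 100; or
- 118 per group were required at 15% attrition and 126 were targeted (with the reason, if there was one), leaving 107 and about 92% power for 5% versus 20%.

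Add a sentence saying that the 5% is a survey prevalence of current use, taken as a proxy for 3-month prescription initiation in the control arm. Report power at 107 per group over assumed control rates on both sides of 5%, as tabulated above.

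The cost is a few sentences and one small table. Enrolment is complete at 381, no additional participants are needed, and neither design nor analysis changes. The correction is best made before outcome results are known. Its only price is that the quoted power becomes openly conditional, and lower if control initiation exceeds 5%.
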